**Methods/design:**

Using the Health Belief Model as a guide, this randomized controlled trial (RCT) will test the efficacy of four sun protection interventions targeting Operating Engineers: a) education only; b) education and mailed sunscreen; c) education and text message reminders; and, d) education, mailed sunscreen, and text message reminders. Participations in the study will be offered during regularly scheduled safety trainings at the Local 324 Training Center. Pre- and post-intervention surveys will be collected to determine changes in sunscreen use and sun burning, the primary dependent variables. The analyses will include: a) paired t-tests to determine changes over time (from pre-intervention to post–intervention) in outcome variables (sunscreen use and burning) separately in the 4 intervention groups, b) Repeated Measures Analysis of Variance (RM-ANOVA) to compare the changes in outcomes across the 4 groups, and c) t-tests on change scores as follow-ups to the RM-ANOVA to determine exactly which groups differ from each other.

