### Measures

#### Independent variables

The independent categorical variables will consist of 3 dummy variables created from the four sun treatment conditions using the education only as the reference group.

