### Data analysis

Descriptive statistics will be computed for all variables at all measurement times. Distributions will be examined and variables will be transformed to normality if needed. The equivalence of the groups on pretest data will be tested using χ^2^ tests of association for categorical variables and Analysis of Variance (ANOVA) for continuous variables. Then analyses to meet the aim will be conducted by paired t-tests, RM-ANOVA, t-tests comparing change scores and by linear regression analyses. If the groups being compared in the RM-ANOVAs differ on the covariates, the analysis will be changed to repeated measures analysis of covariance (RM-ANCOVA) with the differing covariates controlled. Multiple imputation will be used to replace the values of missing data. An intent-to-treat approach will be used so that subjects are considered to be in the condition to which they were randomized despite how much they actually used that type of care. Analyses will be conducted by two-tailed tests with alpha of .05.

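### After a switch to RM-ANCOVA, the named follow-up for deciding which arms differ is still a change-score t-test, which cannot carry the covariates, so the omnibus and pairwise steps come from different models

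*Protocol article*

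**What the plan says.** The abstract of the protocol article (Methods/design) sets out a sequence. The omnibus step is "Repeated Measures Analysis of Variance (RM-ANOVA) to compare the changes in outcomes across the 4 groups". The pairwise step is "t-tests on change scores as follow-ups to the RM-ANOVA to determine exactly which groups differ from each other".

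The Data analysis section repeats the list: "analyses to meet the aim will be conducted by paired t-tests, RM-ANOVA, t-tests comparing change scores and by linear regression analyses". It first tests the arms for baseline differences ("The equivalence of the groups on pretest data will be tested using" chi-square tests or ANOVA) and then gives a conditional rule: "If the groups being compared in the RM-ANOVAs differ on the covariates", then "the analysis will be changed to repeated measures analysis of covariance (RM-ANCOVA) with the differing covariates controlled".

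Under Independent variables, the arms are coded as "3 dummy variables created from the four sun treatment conditions using the education only as the reference group". The article does not say which covariates enter the linear regression, or how the regression relates to the follow-up t-tests.

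**The concern.** The covariate rule is attached to the omnibus analysis alone. The step that decides which arms differ is a named method that has no place for covariates. Once the switch occurs, the named follow-up no longer follows up the model that was fitted.

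The pairwise step carries much of the trial's purpose. The sample size matches a pairwise test (shown in the working). The section on the combined arm asks whether the combination improves on its individual parts, which means combination versus sunscreen and combination versus text messages. The Discussion plans to carry the best interventions into a wider trial. If the plan thinks an imbalance needs controlling, it should be controlled where these questions are answered. Otherwise a report may show an adjusted omnibus result beside unadjusted pairwise results that do not quite agree with it.

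**Working it through.** **1. The plan's own figure.** Inputs from the Power analysis section: 80% power, two-tailed alpha .05, a medium effect (taken as d = 0.5, an assumption, since no number is given), 256 subjects, 20% attrition.
- Two-sample t-test: 63.77, rounded up to 64 per arm; 4 × 64 = 256. Power at 64 per arm is 80.1%.
- Attrition: 256 / 0.80 = 320, as stated.
- An omnibus F-test at f = 0.25 would need only about 179 in total and has 93% power at 256.

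So 256 is reproduced by the pairwise t-test.

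**2. How often the switch occurs.** With k independent covariates each tested at .05, the chance of at least one flag is 1 − 0.95^k. This gives 40% for k = 10, 64% for 20, 75% for 27 and 87% for 40. The article lists many covariates but gives no total, so these counts are assumptions.

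**3. Whether the two steps target the same effect.** They do. With 10 assumed covariates jointly explaining 25% of the variance in change, and a true difference of 0.5 SD, the mean unadjusted estimate was 0.508 and the mean adjusted estimate 0.507. With 27 assumed covariates and 64 per arm, the unadjusted t-test had a type I error of 4.7-5.1%.

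**4. What differs within one trial.** The standard error of an unadjusted pairwise difference is √(2/64) = 0.177 SD.
- *Precision.* When a flagged covariate is prognostic (14-26% of trials, with 3 to 6 prognostic covariates among 27), the standard deviation of the adjusted estimate is about 3-17% smaller than that of the unadjusted one.
- *Verdict on the truly different pair.* Adjusted contrast and t-test disagree on significance in about 5-7% of switched trials (27 independent covariates, 64 per arm, d = 0.5, covariates explaining 20-30% of the variance in change). Over all trials that is 0.75 × 5% to 0.75 × 7%, or about 4-5%.
- *Any of the six verdicts.* With 10 covariates explaining 1%, 9% or 25% of the variance in change, at least one verdict differs in 14%, 19% and 27% of switched trials with one arm at d = 0.5. With no true effect the range is about 9% to 18%.
- *Open contradiction.* A significant adjusted omnibus test with no significant unadjusted pair is rare: 0% to 2.4% of significant adjusted omnibus tests.

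**5. Whether the listed regression closes the gap.** With education only as reference, the three coefficients b1, b2, b3 compare each other arm with education only. The other three pairs are differences bj − bk, with variance Var(bj) + Var(bk) − 2Cov(bj, bk). The model can therefore supply all six contrasts, but nothing in the text assigns it that task or gives it the flagged covariates.

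**6. A condition on the RM-ANCOVA.** With two time points and complete data, a covariate entered only as a main effect leaves the arm-by-time test unchanged. It adjusts the comparison of change only if its interaction with time is in the model. The article does not say that it will be.

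**The case against.** **The two steps might be thought to estimate different effects, or the t-tests to be biased.** A reader might infer this, but the documents do not support it. Arms are randomised and the models are linear, so both analyses target the same mean difference in change, and the t-test keeps its level. Change scores also already remove any covariate effect that is constant over time. Two valid analyses may disagree in one sample without either being wrong. This objection stands and limits the point to coherence and precision.

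**No sentence says the follow-ups stay unadjusted.** That is correct. It is inferred from the named method and the scope of the switching rule. A condensed article may leave post-hoc detail to the full protocol or the analysis plan. But this article does name the pairwise method and does state the switching rule, and the two do not fit together. The point rests on what is stated.

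**The regression could do the job.** It could, for all six pairs; reading it as limited to three comparisons would be wrong. What stands is that the text neither ties it to the pairwise decision nor says it carries the covariates.

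**The size depends on assumptions.** It does. Covariate count, independence and strength are assumed, and the simulations use continuous normal outcomes in place of the five-level items. The larger percentages count any of six verdicts.

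**The next trial's choice may not rest on p-values alone.** Fair: the abstract also names reach and cost as goals.

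**Conclusion.** The point holds as one of internal coherence with a modest cost in precision. As written, covariate control is prescribed for the omnibus test, while the named test for deciding which arms differ cannot carry it. The practical effect is small: about 5-7% of switched trials give a different verdict on the truly different pair, and the standard deviation of the estimate is about 3-17% smaller with adjustment when a flagged covariate is prognostic. These figures rest on the assumptions listed in the working. The text does not support a claim of bias, of inflated type I error at the pairwise step, or of two different estimands. The change is worth making because it costs nothing and replaces a stated method with one that agrees with the omnibus model. How the covariates are selected is a separate issue and is not judged here.

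**What to change.** In Data analysis, and correspondingly in the abstract, replace the follow-up t-tests with a statement of this kind: all six pairwise comparisons (estimate, standard error, p-value) will be contrasts from the same fitted RM-ANOVA or RM-ANCOVA as the omnibus test, with the same covariates, each entered with its covariate-by-time term. Keep the unadjusted change-score t-tests as a sensitivity analysis. If the listed linear regression is meant to supply these contrasts, say so and name its covariates.

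Cost: one sentence. The contrasts are standard output of the model already planned. No new data are needed, and the targets of 256 and 320 do not change.

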## Discussion

The study design is novel in that no studies have compared the individual efficacy of four interventions varying in intensity as well as the average effects of the four interventions. Moreover, no studies have tested the efficacy of mailed sunscreen, which is expected to reduce barriers to use similar to how mailed nicotine replacement reduces barriers to use and enhances smoking quit rates [62]. By incorporating the educational component into regularly scheduled safety trainings that Operating Engineers are already attending for their job, it is expected that participation rates will be high. The setting is novel in that work site interventions have not been tested among Operating Engineers who have high sun burning rates. This proposal is timely in that the new federal Affordable Care Act (ACA) [63] contains numerous provisions to encourage prevention including worksite initiatives as most adults spend almost one-third of their time in the workplace.

Taking the best interventions from this trial, we have the possibility of developing a wider scale trial in conjunction with the International Training Center, which services North America (including the United States, Mexico, and Canada). The intervention may be even more beneficial to southern states with hotter climates than Michigan. Wide scale dissemination of an efficacious sun protection intervention has the potential to decrease sun burning and skin cancer rates among this population.

## Consent

Written informed consent was obtained from the participants for publication of this report.

## Abbreviations

RM-ANOVA: Repeated measures analysis of variance; UV: Ultra violet; RCT: Randomized controlled trial; USFDA: U.S. Food and Drug Administration; USPSTF: U.S. Preventive Services Task Force; AAD: American Academy of Dermatology; SPF: Sun protection factor; CES-D-SF: Center for Epidemiologic Studies/Depressed Mood Scale; BMI: Body mass index; AUDIT-C: Alcohol Use Disorders Identification Test-Hepatitis C; ANOVA: Analysis of variance; RM-ANCOVA: Repeated measures analysis of covariance; ACA: Affordable Care Act
